**Methods:**

We will pilot the implementation of birth testing by HIV DNA PCR, as well as two POC testing systems (Xpert HIV-1 Qual [Xpert] and Alere q HIV-1/2 Detect [Alere q]), on specimens collected from Kenyan infants at birth (0 to 2 weeks) and 6 weeks (4 to < 24 weeks) postnatal. The formative phase will inform optimal implementation of birth testing and two POC testing technologies. Qualitative interviews with stakeholders (providers, parents of HIV-exposed infants, and community members) will assess attitudes, barriers, and recommendations to optimize implementation at their respective sites. A non-blinded pilot study at four Kenyan hospitals (*n* = 2 Xpert, *n* = 2 Alere q platforms) will evaluate infant HIV POC testing compared with standard of care HIV DNA PCR testing in both the birth and 6-week windows. Objectives of the pilot are to assess uptake, efficiency, quality, implementation variables, user experiences of birth testing with both POC testing systems or with HIV DNA PCR, and costs.

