## Methods

### Study design

In this feasibility study, the new birth EID testing timepoint and two POC infant diagnostic platforms will be implemented on a pilot scale in Kenya. Xpert and Alere q HIV POC platforms will be introduced at four Kenyan government hospitals, for birth and 6-week testing time points. This 18-month study was initiated as a supplement to a parent study (R01HD076673) implementing and evaluating the HIV infant tracking system (HITSystem) [30]. The four hospitals designated as study sites are government hospitals with medium to high patient volume, and geographic variation: two in Kisumu County, one in Nakuru County, and one in Mombasa County. Estimated rates of mother to child transmission of HIV in these three counties in 2015 were 20%, 5%, and 18%, respectively [31]. Phase 1 is a 6-month formative phase in which we will conduct qualitative interviews with parents, providers, and community members to assess stakeholder attitudes toward birth and POC testing and barriers to acceptance or uptake. Feedback will be used to refine operational plans with regard to feasibility and acceptability. Phase 2 is a 12-month feasibility pilot of the two new POC testing strategies. The 12-month implementation period allows time for providers to adopt the new practices and to monitor any fluctuations in uptake or acceptability during this extended period. POC HIV testing will be conducted in parallel with standard laboratory-based HIV DNA PCR, targeting sample collection at birth (0 to 2 weeks) and at 6 weeks (4 to < 24 weeks).

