### Phase 2: intervention

#### Study design

We will pilot the implementation of POC and birth testing at four government hospitals over a 12 month period. The four study sites will be randomized, using a random number generator, to pilot one of the two POC systems (Xpert HIV-1 Qual for HIV RNA or Alere q HIV-1/2 Detect). SOC diagnostic testing (HIV DNA PCR test on DBS samples) will be conducted in parallel at all study sites, including the newly introduced birth testing time point. Patient flow in the pilot is diagrammed in Fig. 1.

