##### POC platform performance

Assessment of both the Xpert and Alere q HIV POC platforms will include evaluation of testing reliability (Table 1). Measures to be tracked include number of failed tests (and wasted cartridges), and number of missed opportunities to engage infants with POC testing due to documented machine breakdown, machine error, or cartridge stockout. The anticipated number of HIV-positive infants identified is too small to support robust sensitivity or specificity calculations, but we will track concordance between test results from each POC platform and the corresponding HIV DNA PCR results.

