### Statistical analysis

This study is designed to gather preliminary outcome data to inform implementation guidance and pilot data for a subsequent larger study. We anticipate mean monthly enrollment per study site of approximately 15 eligible participants, yielding an estimated total enrollment of 720 mother-infant pairs by the end of the 12-month intervention phase. Reductions in study participation are expected to result from documented transfer to other facilities, loss to follow-up, miscarriage, and infant mortality prior to testing. Nonetheless, we anticipate ample power to describe and compare outcomes of birth testing and between POC and PCR testing strategies to estimate effect sizes and an intracluster correlation coefficient (ICC) to inform future sample size and power calculations.

Categorical variables will be presented as proportions, and continuous variables as means (SD) or medians (IQR) depending on the distribution of data. Quantitative measures compared across POC platforms or between POC and HIV DNA PCR testing methods will be analyzed using parametric and non-parametric (Exact or Wilcox and Rank-sum) tests.

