### Study status

We have conducted formative interviews with stakeholders (providers, HIV-positive parents, and community members). We began mother-infant enrollment in the study in June of 2017. During the initial 6 months, participant enrollment and full implementation of the pilot were limited by external challenges (prolonged national nurses’ strike and Alere q manufacturer’s cartridge stock-out), which were resolved, setting the stage for normal operations. Participant enrollment is ongoing and expected to conclude in December 2018. We plan to report study results to a national technical working group on implementation of birth and POC testing in Kenya, to the Ministry of Health, and to administrators of the participating facilities. Data will be published in peer-reviewed scientific journals.

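### Xpert and Alere q are allocated to four hospitals, two each, but the planned tests across platforms have no site term, so a hospital difference can easily be mistaken for a platform difference

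*Protocol article*

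**What the plan says.** The unit of allocation is the hospital. Phase 2, Study design: "The four study sites will be randomized, using a random number generator, to pilot one of the two POC systems". The abstract gives the numbers: "A non-blinded pilot study at four Kenyan hospitals (*n* = 2 Xpert, *n* = 2 Alere q platforms". The size figures are in Statistical analysis: "mean monthly enrollment per study site of approximately 15 eligible participants", and an "estimated total enrollment of 720 mother-infant pairs by the end of the 12-month intervention phase".

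The same section fixes the analysis: "Quantitative measures compared across POC platforms or between POC and HIV DNA PCR testing methods will be analyzed using parametric and non-parametric" tests, with exact, Wilcoxon and rank-sum tests given in brackets. No site effect, cluster adjustment or site-level analysis is named. The section also plans to estimate an ICC, but only to help size later studies.

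The sites are spread over three counties. The Study design section says: "Estimated rates of mother to child transmission of HIV in these three counties in 2015 were 20%, 5%, and 18%, respectively".

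For platform reliability, the POC platform performance section says: "Measures to be tracked include number of failed tests (and wasted cartridges", together with counts of missed opportunities. Table 1 also words these as numbers. The Discussion speaks of a test failure rate.

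**The concern.** With two hospitals per platform, everything that distinguishes one pair of hospitals from the other (volume, staffing, courier links, local practice) is carried into the platform contrast. A test that treats infants as independent counts the variation between infants but not the variation between hospitals. Its p-value is therefore too small whenever hospitals differ for reasons unrelated to the device.

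The protocol expects clustering, since it plans to estimate an ICC, but does not carry that expectation into its own tests across platforms. What is at stake is how the results are read. They are to go to a national technical working group and the Ministry of Health, and the Discussion hopes they will guide others who are considering investment in POC equipment. A platform p-value that mainly reflects which hospitals received which machine could influence such a decision.

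**Working it through.** **Inputs from the protocol.** Four sites, two per platform; about 15 pairs per site per month; 12 months. Check of the stated total: 15 × 4 × 12 = 720, which agrees. This gives 15 × 12 = 180 per site and 360 per platform.

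**Assumptions.** Two-sided alpha 0.05; ICC from 0.001 to 0.10; equal site sizes. The protocol states no alpha and no ICC. It expects losses before testing, without giving a rate, and reports limited enrolment in the first six months. Site sizes of 90 and 60 are therefore shown as well.

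**Unit of analysis.** The protocol does not name it. Four sites can be split two and two in C(4,2) = 6 ways, so an exact or rank-sum test on four site values has a smallest two-sided p of 2/6 = 0.33. Such tests could never be significant at site level, so naming them makes sense only for infants.

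**True type I error of the infant-level test.** The design effect is DE = 1 + (m − 1) × ICC, with m infants per site. With no platform effect, the naive z statistic has standard deviation √DE, so the rejection probability is 2 × [1 − Φ(1.96/√DE)].

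- m = 180, ICC 0.01: DE = 1 + 179 × 0.01 = 2.79; 1.96/1.670 = 1.173; error 0.241. Effective number per platform: 360/2.79 = 129.
- m = 180, ICC 0.05: DE = 9.95; 1.96/3.154 = 0.621; error 0.534. Effective number per platform: 360/9.95 = 36.

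| ICC (assumed) | 180 per site | 90 per site | 60 per site |
|---|---|---|---|
| 0.001 | 7.1% | 6.0% | 5.7% |
| 0.005 | 15.5% | 10.3% | 8.5% |
| 0.01 | 24.1% | 15.4% | 12.0% |
| 0.02 | 36.0% | 24.0% | 18.4% |
| 0.05 | 53.4% | 40.1% | 32.4% |
| 0.10 | 65.2% | 53.3% | 45.6% |

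A simulation of 4 sites × 180 infants with no platform effect (4,000 runs) agrees. At ICC 0.01, 0.05 and 0.10, Fisher's exact test (80% base rate assumed) rejects in 22%, 52% and 65% of runs, and the rank-sum test in 24%, 52% and 64%.

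**One unusual hospital.** Suppose three sites have 80% on some measure and one is lower, with no device effect. The platform difference is then half that site's shortfall. With 360 per platform, the chance of a significant result is 13% for a 5-point shortfall, 36% for 10, 66% for 15 and 87% for 20.

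**Would a site-level test rescue the comparison?** A t-test on four site values has 2 degrees of freedom and a critical value of 4.30. At an 80% base rate, the standard deviation of a site proportion is √(0.16 × DE/180), which is 0.050 at ICC 0.01 and 0.094 at ICC 0.05. The standard error of the platform difference equals this, since √(1/2 + 1/2) = 1. Power for a 20-point difference is about 57% and 24% respectively; for a 10-point difference it is 22% and 10%. Four hospitals therefore support description of the platform contrast and little more.

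**The case against.** The case for leaving the text alone is that this is a pilot meant to give preliminary data. None of the listed objectives is a head-to-head test of Xpert against Alere q. The power statement names birth testing and POC versus PCR, not the platforms. No significance threshold or rule for choosing a platform is given, and the unit of analysis is inferred. All of that is true, and it limits the seriousness of the point. It does not remove it, because the analysis sentence explicitly covers comparisons across platforms and names tests that do not fit the allocation.

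Several stronger readings are tempting but not supported:

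- A reader might infer that any ordinary site difference will be declared a platform difference. The figures do not show this: a 5-point shortfall at one site is flagged 13% of the time, and at ICC 0.001 the error is only 7%.
- A reader might extend the point to POC versus HIV DNA PCR. Both are run in parallel at every site, so platform allocation does not confound that comparison.
- A reader might take the county transmission rates as proof that platform outcomes differ. They show that the settings are unlike, but transmission is not a platform outcome, and the article does not report which hospital received which platform.
- A reader might infer that raw counts will favour Alere q because of its cartridge stock-out. The Study status section says that "participant enrollment and full implementation of the pilot were limited by external challenges", naming a nurses' strike and the stock-out, but gives no stock-out duration from which to compute unequal exposure. Missed opportunities from stock-outs are themselves a tracked outcome. Machine use is logged, the Confidentiality section promises aggregates and ratios, and the Discussion lists a failure rate. What remains is a wording mismatch, not a bias.

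**Conclusion.** The point holds for Xpert versus Alere q only. Platform is allocated by hospital, two per platform, and the named tests take no account of hospital. On the inferred infant-level reading, a nominal 5% test has a true error of about 7% at ICC 0.001, 15% at 0.005, 24% at 0.01 and 53% at 0.05 with 180 per site. With 60 per site it is 12% at ICC 0.01 and 32% at 0.05. The exact size rests on the assumed ICC and alpha and on the number of infants finally tested. The direction does not: the error exceeds 5% at every positive ICC considered. No valid exact test on four sites can fall below p = 0.33, so no change of test makes this contrast confirmatory. It should be fixed, but it does not undermine the pilot's main purposes.

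**What to change.** In Statistical analysis, state that Xpert versus Alere q is descriptive, with no p-values. Show each measure site by site and then by platform, and say that platform cannot be separated from hospital with two sites each. This point gives no reason to change the tests for POC versus HIV DNA PCR, so keep them, but write that comparison as a separate sentence.

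As a minor alignment, report failed tests over tests run and missed opportunities over infants presenting. Table 1 and POC platform performance then agree with the failure rate in the Discussion. The logs already planned should supply the denominators.

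The cost is wording only, with no change to data collection or sample size. The downside is that platform p-values are given up.

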### Study status

We have conducted formative interviews with stakeholders (providers, HIV-positive parents, and community members). We began mother-infant enrollment in the study in June of 2017. During the initial 6 months, participant enrollment and full implementation of the pilot were limited by external challenges (prolonged national nurses’ strike and Alere q manufacturer’s cartridge stock-out), which were resolved, setting the stage for normal operations. Participant enrollment is ongoing and expected to conclude in December 2018. We plan to report study results to a national technical working group on implementation of birth and POC testing in Kenya, to the Ministry of Health, and to administrators of the participating facilities. Data will be published in peer-reviewed scientific journals.

## Discussion

The effectiveness of ART in HIV-infected infants is optimal when HIV is diagnosed early, so that treatment can be initiated before a peak in mortality observed between 2 and 3 months [16]. For this reason, Kenyan government guidance issued in 2016 recommends adding birth HIV DNA PCR testing to the standard regimen of PCR tests at 6 weeks, 6 months, and 12 months [19]. However, to date, this is only a provisional recommendation pending pilot data to inform national scale-up. This study will contribute needed pilot data to inform decision making for birth testing with traditional HIV DNA PCR or with POC strategies. Notably, recent data from South Africa suggest uptake of repeat testing at 6 or 10 weeks of age may be diminished among infants already diagnosed HIV-negative at birth [34]. A reduction in retesting rates compromises detection of intrapartum transmissions, thus the impact of birth testing on repeated testing at 6 weeks is an important concern for governments considering policy changes. In addition to assessing uptake and acceptability of the new testing time point and testing strategy (POC), this pilot and feasibility study is designed to assess retest rates for infants tested within the birth window to better understand implications for the Kenyan context.

POC testing also offers potential to improve EID system efficiency in low resource settings where there are multiple delays inherent in the laboratory-based HIV DNA PCR testing process. Sample testing in the clinic setting potentially facilitates mother notification of infant HIV status on the same day as test. To fully realize the POC technology’s potential at the true point of care, cadres of clinical providers must be trained to perform diagnostic procedures outside of traditional clinical duties. Therefore, in addition to traditional laboratory personnel, our pilot study includes training nurses to conduct POC testing within the Maternity and MCH settings. This pilot will solicit provider feedback regarding issues of patient flow, interdepartmental collaboration, and provider workload, while identifying potential barriers to this task-shifting approach during larger scale-up. Other performance measures reflecting the utility of POC platforms—such as user friendliness, equipment durability, test failure rate, costs of maintenance, and frequency of cartridge stockouts—will likely affect the consistency of testing operations and missed opportunities for diagnosis. This pilot study will track these variables and thus supply preliminary feasibility data to inform effective and sustainable POC interventions for larger future studies.

These novel data on implementation outcomes and clinical impact of birth HIV testing with POC and PCR testing strategies are timely given the movement toward more rigorous EID in low resource countries. Implementation and user satisfaction data from the two approved POC platforms, GeneXpert and Alere q, may also guide other groups considering investment in POC scale-up. By providing parameters to estimate effect size and intraclass correlation, these results will facilitate the design of properly powered pragmatic trials to evaluate the impact of birth and POC HIV testing in Kenya. These timely data may also facilitate wider adoption of 2016 EID guidelines issued by WHO and the government of Kenya to accelerate infant testing within the existing PCR infrastructure, while bridging the birth testing strategy to implementation of POC testing technologies.

## Abbreviations

ART: Antiretroviral therapy
CCC: Comprehensive care center
DBS: Dried blood spot
EID: Early infant diagnosis
HIV: Human immunodeficiency virus
IQR: Interquartile range
MCH: Maternal and child health
PCR: Polymerase chain reaction
PMTCT: Prevention of mother to child transmission
POC: Point-of-care
SD: Standard deviation
SOC: Standard-of-care
TAT: Turnaround time
VL: Viral load
WHO: World Health Organization
